## Statistical Analysis Method

1. **Definition of Analysis Sets**

### Efficacy Analysis Set

Subjects who meet the inclusion/exclusion criteria, have been enrolled in this study, received the investigational product at least once, and have had their HbA1c level collected post-baseline will be included in the efficacy analysis set.

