- Concomitant medications: During the study period after Visit 1 (Baseline, Day 0), collect information on all concomitant medications taken consistently for more than 3 months, including medications for the treatment of Type 2 Diabetes. This includes the drug name (generic or brand name), reason for administration, duration of administration (start date, end date, ongoing status), single dose amount/unit, daily administration frequency, route of administration, any dosage changes or discontinuation, and reasons for changes or discontinuation.

1. Laboratory tests are collected if conducted as part of routine clinical practice. If there are HbA1c results within 4 weeks prior to Visit 1 (Baseline, Day 0) or other test results within 3 months prior to Visit 1, these results can be used in place of the laboratory tests at Visit 1 (Baseline, Day 0). Cardiovascular disease complication risk (ASCVD risk) will be assessed using the ASCVD 2013 Risk Calculator from AHA/ACC. Analysis will be conducted after the study is completed based on information collected in the eCRF (gender, age, systolic blood pressure, total cholesterol, HDL-C, hypertension medication use, diabetes diagnosis, and smoking status). In the test group, the automatic calculation feature within the Well Check app allows investigators (responsible physicians) to input cholesterol and blood pressure values for use during patient consultations.

| Main Laboratory Tests | HbA1c, FPG(FBS) |
| --- | --- |
| Other Laboratory Tests  (Blood Tests) | Total Cholesterol, HDL-C, LDL-C, Triglyceride, ALT, AST, γ-GTP, Creatinine, e GFR, UACR, UGCR |

1. At the close-out visit, a written survey will be conducted to assess the experiences of both the medical staff (responsible physicians) and the subjects with using Well Check.

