   - Former Smoker: Has smoked ≥ 5 packs (100 cigarettes) in a lifetime, but no smoking in the last 30 days
   - Non-smoker: Has smoked < 5 packs (100 cigarettes) in a lifetime
2. Lifestyle Habits (Dietary Habits): Irregular meals, overeating, excessive intake of carbohydrate/sugar, excessive fat intake, excessive salt intake
3. Lifestyle Habits (Exercise Habits): Types of exercise (walking, aerobic exercise, strength training), weekly exercise frequency, exercise intensity (less than 30 minutes, up to 1 hour, long duration)
4. **Physical Measurement**

Collect weight and BMI at every visit, with BMI automatically calculated in the CRF using height and weight. Collect height once at Visit 1 (Baseline, Day 0).

1. **Vital Signs**

At every visit, the following vital signs will be collected:

- Blood pressure (systolic/diastolic)
- Pulse Rate

Blood pressure and pulse rate should be measured in a quiet environment after at least 5 minutes of rest in a chair with a backrest. The subject should refrain from smoking, alcohol, and caffeine intake for at least 30 minutes prior to measurement, if possible.

1. **Body Composition Analysis**

For the feasible institutions capable of conducting these measurements, collect the following items at Visit 1 (Baseline, Day 0), Visit 3 (Follow-up visit, 12 weeks), and Visit 5 (Close-out visit, 24 weeks).

- Body composition analyzer indices: Skeletal muscle mass, body fat mass, body fat percentage, muscle mass, waist/hip circumference, body water, intracellular water, extracellular water, extracellular water ratio, abdominal fat percentage, etc.

1. **Prior/Concomitant Medications**

For prior medications, collect information on diabetes treatments administered within 4 weeks before Visit 1 (Baseline, Day 0). For concomitant medications, collect information on all concomitant medications taken for 3 months or more during the study period after Visit 1 (Baseline, Day 0), including those for the treatment of Type 2 Diabetes.

- Drug Name (Brand Name)
- Dosage and Administration (Dose per administration, unit, frequency, route)
- Duration of Administration (Start date, end date, ongoing status)
- Purpose of Administration
- Reason for Dose Adjustment or Discontinuation (if applicable)

1. **Laboratory Tests**

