# Evaluation Criteria and Methods, and Statistical Analysis Methods

## Endpoints

1. **Efficacy Endpoints**
2. **Primary Efficacy Endpoint**

- Percent change and change of HbA1c at 24 weeks compared to baseline

1. **Secondary Efficacy Endpoints**
   1. Percent change and change of FPG at 6, 12, 18, and 24 weeks compared to baseline
   2. Percent change and change in HbA1c at 6, 12, and 18 weeks compared to baseline
   3. Proportion of subjects achieving HbA1c < 7% at 6, 12, 18, and 24 weeks compared to baseline
   4. Proportion of subjects achieving HbA1c < 6.5% at 6, 12, 18, and 24 weeks compared to baseline
   5. Proportion of subjects achieving therapeutic response [change in HbA1c (baseline HbA1c – HbA1c at each evaluation time point) > 0.5% or HbA1c < 7%] at 12 and 24 weeks compared to baseline
   6. Change in blood pressure (systolic and diastolic) at 6, 12, 18, and 24 weeks compared to baseline
   7. Change in BMI and weight at 6, 12, 18, and 24 weeks compared to baseline
   8. Proportion of subjects with a reduction of 5% or more in weight and BMI at 6, 12, 18, and 24 weeks compared to baseline
2. **Exploratory Endpoints**
3. Change in lipid levels (total cholesterol, LDL-C, HDL-C, triglycerides) at 6, 12, 18, and 24 weeks compared to baseline
4. Change in liver function markers (AST, ALT, γ-GTP) at 6, 12, 18, and 24 weeks compared to baseline
5. Change in renal function markers (e-GFR, UACR, UGCR) at 6, 12, 18, and 24 weeks compared to baseline
6. Change in body composition analyzer indicators (skeletal muscle mass, body fat mass, body fat percentage, muscle mass, waist/hip circumference, body water, intracellular water, extracellular water, extracellular water ratio, abdominal fat percentage) at 12 and 24 weeks compared to baseline
7. Change in cardiovascular disease complication risk (ASCVD risk) at 12 and 24 weeks compared to baseline
8. **Safety Endpoints**
9. Laboratory tests, vital signs, physical examination results

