### Safety Analysis Set

Subjects who meet the inclusion/exclusion criteria, have been enrolled in this study, received the investigational product at least once according to the approved indications, and have undergone safety evaluations will be included in the safety analysis set.

1. **Methods of Analysis**
2. **General Principles**

Continuous variables will be presented as descriptive statistics (number of subjects, mean, standard deviation, median, minimum, maximum), and categorical variables will be presented as frequencies and percentages. Unless otherwise specified, all tests will be two-sided with a significance level of 5%. All p-values will be reported to a maximum of three decimal places. If not exactly divisible, values will be rounded to two decimal places, rounding up at the third decimal place.

If missing data is minimal and evenly distributed, a complete-case analysis will be considered; multiple imputation methods will be employed if missing data is substantial or disproportionately distributed between groups. Sensitivity analyses will also be performed to ensure the robustness and validity of conclusions under various missing-data scenarios.

1. **Demographic and Baseline Characteristics**

For the demographic data (age, gender, etc.) and baseline characteristics of the study subjects, continuous variables will be presented as mean, standard deviation, median, minimum, and maximum values, while categorical variables will be presented as frequency and percentage.

To assess baseline comparability between intervention and control groups, standardized mean differences (SMDs) will be calculated for key baseline characteristics, including age, sex, HbA1c, BMI, and diabetes duration. Variables exhibiting significant imbalance between groups (SMD > 0.1) will be included as covariates in subsequent analyses.

1. **Efficacy Endpoints**

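### The only efficacy set requires a post-baseline HbA1c, so observed weight, BMI and other follow-up data can be dropped from efficacy analyses that do not use HbA1c

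*Protocol*

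**What the plan says.** Section 7.2 of the protocol defines two analysis sets. The efficacy set takes eligible enrolled subjects who "received the investigational product at least once, and have had their HbA1c level collected post-baseline will be included in the efficacy analysis set". The safety set has no HbA1c requirement; beyond eligibility, enrolment and product use it asks that subjects "and have undergone safety evaluations will be included in the safety analysis set".

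Section 7.1 lists many efficacy endpoints that are not HbA1c. The secondary endpoints include "Percent change and change of FPG at 6, 12, 18, and 24 weeks compared to baseline", "Change in blood pressure (systolic and diastolic) at 6, 12, 18, and 24 weeks compared to baseline" and "Change in BMI and weight at 6, 12, 18, and 24 weeks compared to baseline". The exploratory endpoints, under the same efficacy heading, include "Change in lipid levels (total cholesterol, LDL-C, HDL-C, triglycerides) at 6, 12, 18, and 24 weeks compared to baseline", together with liver and renal markers, body composition and ASCVD risk. The paragraphs of section 7.2 on primary, secondary and exploratory endpoints state the model but not the population.

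On availability, the laboratory footnote to the Schedule for Data Collection says "Laboratory tests are collected if conducted as part of routine clinical practice". Section 4.3 adds that the study itself makes no visit, test or treatment mandatory. For physical measurements, section 4.4 says "Collect weight and BMI at every visit".

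**The concern.** A membership rule that suits the primary endpoint is also the only rule available for endpoints that have nothing to do with HbA1c. A weight recorded at week 24 is a valid observation of the weight endpoint whether or not the clinic ordered an HbA1c. Under the rule as written, that weight is not analysed for efficacy if the patient has no HbA1c after baseline.

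Two things are at stake. The first is observed data lost without a reason connected to the endpoint; weight and blood pressure are among the effects that section 4.1 says the trial is designed to confirm. The second is selection. Whether a patient has any HbA1c after baseline depends partly on what the physician does after the clinic has been allocated. Section 4.4 asks physicians in the test arm to review patients' self-records, enter blood results where tests are done and evaluate ASCVD risk at visits. Control physicians give routine care without the physician web. Testing frequency could therefore differ by arm, and the set would carry that difference into endpoints that do not need it.

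**Working it through.** **1. Which population applies.** Section 7.2 offers an efficacy set and a safety set. The secondary and exploratory endpoints are efficacy endpoints by their heading in section 7.1, and their analysis paragraphs name no set. The efficacy set is the only one that fits. This is an inference, but the text offers no competing candidate.

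**2. Whether a patient can have other data but no HbA1c.** No test is mandatory, laboratory values come from routine care only, and Visits 2 and 4 may be skipped or done by telephone. A patient seen at week 12 or week 24 with weight and blood pressure recorded but no HbA1c ordered is therefore possible. The gate asks for one HbA1c at any time after baseline, so a patient with a week-12 value and none at week 24 stays in. Only patients with no HbA1c throughout follow-up are removed.

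**3. Whether anything brings them back.** The missing-data rule in section 7.2 allows complete-case analysis or multiple imputation, but does not say that it extends to subjects outside the set. For the endpoints at issue the excluded values are observed, so imputation is not the remedy.

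**4. Where else the data are analysed.** Section 7.2 models change in vital signs and laboratory tests at 6, 12, 18 and 24 weeks as safety endpoints, presumably in the safety set. That covers blood pressure, FPG, lipids and the other laboratory values. No weight, BMI or body-composition analysis is described there.

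**5. Size in precision (illustration).** The documents give no share of patients without any post-baseline HbA1c. The planning inputs in section 3.2 are ICC 0.02 and 20 patients per centre; the synopsis gives 24 institutions. The plan's own design effect reproduces: 1 + (20 − 1) × 0.02 = 1.38, and 274 × 1.38 = 378. The target of 480 equals 24 × 20.

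For a mean, variance is proportional to [1 + (m − 1) × ICC] / N, with m = N / 24. Assume that 432 of 480 patients (90%) have follow-up weight, and that the ICC of 0.02 holds for weight.

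- All 432 kept: m = 18, 1.34 / 432 = 0.003102.
- 24 removed (5.6%): N = 408, m = 17, 1.32 / 408 = 0.003235; SE ratio √(0.003235 / 0.003102) = 1.021.
- 48 removed (11%): N = 384, m = 16, 1.30 / 384 = 0.003385; SE ratio √1.091 = 1.045.
- 72 removed (16.7%): N = 360, m = 15, 1.28 / 360 = 0.003556; SE ratio √1.146 = 1.071.

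The standard error for weight rises by about 2% to 7% over this assumed range.

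**6. Size in bias (illustration).** If a fraction f_t of test patients and f_c of control patients is excluded, and the excluded differ from those kept by D standard deviations in both arms, the between-group difference shifts in absolute size by (f_c − f_t) × D. With 5% and 20% excluded, D = 0.25 gives 0.15 × 0.25 = 0.04 SD and D = 0.5 gives 0.15 × 0.5 = 0.08 SD (0.0375 and 0.075 before rounding). With 5% and 10%, the shifts are 0.01 and 0.03 SD (0.0125 and 0.025). All of these fractions and differences are assumptions.

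**The case against.** The strongest case against this point has four parts.

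First, a reader might infer that weight and blood pressure are assured at each visit while HbA1c is left to chance. The documents do not support that contrast. The Schedule for Data Collection gives physical measurement, vital signs and laboratory tests the same marks: planned at Visits 1, 3 and 5 and bracketed at Visits 2 and 4. The footnote on vital signs also has results collected if they exist. All of these variables come from routine care, and HbA1c is listed as a main laboratory test. What remains is that the variables can be missing separately, which is enough for the rule to discard data.

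Second, a reader might apply one patient count to every non-HbA1c endpoint. That does not follow. FPG, lipids, liver and renal markers are laboratory tests too, and ASCVD risk needs total cholesterol and HDL-C, so a patient without HbA1c may well lack these and nothing observed would be lost. Body composition is measured only at clinics able to do it. The illustration is plausible for weight and BMI, and for blood pressure in its efficacy analysis only.

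Third, blood pressure and laboratory values are modelled again as safety endpoints without the HbA1c condition. This stands, so those data do not vanish from reporting. It does not repair the efficacy analyses, and it could give two estimates of the same variable from two populations.

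Fourth, populations for individual endpoints are often left to a statistical analysis plan. Here, however, the protocol states a membership rule, and a later plan that followed it would inherit the problem.

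**Conclusion.** The point holds as a flaw in a stated rule, of modest size. On the natural reading, patients with observed follow-up on another endpoint but no HbA1c at any visit after baseline are removed from secondary and exploratory efficacy analyses that do not use HbA1c. The practical effect falls mainly on weight and BMI, which have no alternative analysis described. For blood pressure and laboratory endpoints the efficacy analysis is affected, but the safety analysis retains the data.

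Precision is a small matter: about 4.5% on the standard error for weight if 11% of patients with weight data had no post-baseline HbA1c, and about 2% to 7% for losses of 5.6% to 16.7%. Selection by arm is the better reason to act, with an illustrative shift of up to about 0.08 SD under deliberately unequal exclusion. These figures rest on assumed shares, since the documents give none. They do not show that a bias will occur, nor that the primary analysis or the sample size is wrong.

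**What to change.** In section 7.2, Efficacy Analysis Set, limit the HbA1c condition to the HbA1c endpoints. State that each other efficacy endpoint is analysed by clinic allocation in all eligible enrolled subjects with data on that endpoint, with missing values handled by the model or by the imputation already provided for in section 7.2. Keep the present set as a sensitivity analysis. The secondary and exploratory paragraphs should then name the population they use.

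The cost is a short change of text. No new data are needed and no sample-size figure changes. Denominators will differ between endpoint tables and must be shown in each. Selection on whether the endpoint itself was measured remains: the change reduces post-allocation selection but does not eliminate it.

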### Safety Analysis Set

Subjects who meet the inclusion/exclusion criteria, have been enrolled in this study, received the investigational product at least once according to the approved indications, and have undergone safety evaluations will be included in the safety analysis set.

1. **Methods of Analysis**
2. **General Principles**

Continuous variables will be presented as descriptive statistics (number of subjects, mean, standard deviation, median, minimum, maximum), and categorical variables will be presented as frequencies and percentages. Unless otherwise specified, all tests will be two-sided with a significance level of 5%. All p-values will be reported to a maximum of three decimal places. If not exactly divisible, values will be rounded to two decimal places, rounding up at the third decimal place.

If missing data is minimal and evenly distributed, a complete-case analysis will be considered; multiple imputation methods will be employed if missing data is substantial or disproportionately distributed between groups. Sensitivity analyses will also be performed to ensure the robustness and validity of conclusions under various missing-data scenarios.

1. **Demographic and Baseline Characteristics**

For the demographic data (age, gender, etc.) and baseline characteristics of the study subjects, continuous variables will be presented as mean, standard deviation, median, minimum, and maximum values, while categorical variables will be presented as frequency and percentage.

To assess baseline comparability between intervention and control groups, standardized mean differences (SMDs) will be calculated for key baseline characteristics, including age, sex, HbA1c, BMI, and diabetes duration. Variables exhibiting significant imbalance between groups (SMD > 0.1) will be included as covariates in subsequent analyses.

1. **Efficacy Endpoints**

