| **Target Number of Subjects** | Approximately 480 subjects (considering about 20% dropouts to ensure statistical significance) |
| **Duration of Study** | - Expected Total Duration of Study: Date of first IRB approval to December 31, 2026   (may be subject to change depending on the subject enrollment rate)   - Study Period per Subject: Approximately 24 weeks (6 months) |
| **Investigational Software** | Digital healthcare smartphone application ‘Well Check’ |

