## Study Completion and Withdrawal/Dropout

1. **Subject’s Completion and Termination of Study Participation**

A subject is considered to have completed the study upon completing the follow-up visit procedures at the 24-week point after their first visit (baseline). The study is deemed complete when the last subject finishes their study participation.

1. **Subject’s Withdrawal/Dropout of Study Participation**

Subjects can discontinue their participation in the study at any time at their discretion. The investigator or sponsor can also withdraw/drop a subject’s participation at any time for safety, behavioral, or administrative reasons. The following are conditions under which a subject might be withdrawn/dropped from the study, and the investigator shall enter the collected study data into the eCRF up to the point of withdrawal/dropout:

1. A subject not meeting the inclusion/exclusion criteria was discovered during the clinical study
2. Withdrawal by subject (or his/her legal representative)
3. Non-Compliance with Investigational Product

: Subjects do not agree to or follow the investigator’s instructions related to the investigational software.

1. Lost to follow-up

: Subjects cannot be contacted for follow-up.

1. Physician Decision

If a subject is withdrawn/drops out, the investigator must notify the sponsor and make every effort to complete the end-of-study evaluation. The reasons for withdrawal/dropout must be documented in the source document and the eCRF.

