## Measures to Protect the Safety of Subjects

Study sites should have the facilities and specialized personnel necessary to conduct this study and should be fully prepared to properly conduct the study.

The investigator should thoroughly check the health of each subject prior to enrollment into the study to ensure that subjects are eligible to participate in the study. Also, the investigator must thoroughly understand the study protocol and conduct the study accordingly.

The treatment and care of the subjects' conditions should be conducted independently of this study and should continue based on clinical judgment during and after the study period.

This study does not present any risks beyond the routine treatment provided in a clinical setting. Therefore, there are no additional risks related to the study, and no extra compensation for the subjects is necessary. Both the Medical Service Act and the professional liability insurance of the principal investigator and relevant institutions provide sufficient protection for both study subjects and participating investigators.

Since this study does not provide investigational drugs to the subjects, any drug-related compensation will follow the existing legal responsibilities for the drugs.

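### The safety set excludes exposed subjects later found ineligible and applies an approved-indications test that is undefined for an app

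*Protocol*

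**What the plan says.** Section 7.2 of the protocol sets three conditions for the safety set, beyond enrolment itself:

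- **Eligibility:** "Subjects who meet the inclusion/exclusion criteria, have been enrolled in this study".
- **Use within indications:** "received the investigational product at least once according to the approved indications".
- **Evaluation:** subjects must also "have undergone safety evaluations will be included in the safety analysis set".

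The efficacy set in the same section has the same eligibility condition. Its exposure condition is plainer: "received the investigational product at least once, and have had their HbA1c level collected post-baseline". It has no approved-indications test.

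The Synopsis gives the investigational software as Well Check, a "Digital healthcare smartphone application". Section 3.5 lists withdrawal reasons. One is "A subject not meeting the inclusion/exclusion criteria was discovered during the clinical study". Another, non-compliance with the investigational product, is explained as not following "instructions related to the investigational software". Section 8.8 adds that "this study does not provide investigational drugs to the subjects".

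**The concern.** A safety population is normally built on exposure: whoever received the intervention is counted, whatever is learned later about eligibility. Here the rule conditions on eligibility. Section 3.5 shows that the protocol expects some subjects to be found ineligible after they have started. It has their data entered in the eCRF up to withdrawal and asks the investigator to try to complete the final evaluation. The safety-set definition then leaves those data unused.

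What is at stake is the completeness of the safety account. Section 7.2 (Laboratory Tests) promises frequencies of clinically significant abnormalities and a listing of the subjects who have them. A subject enrolled despite a renal, hepatic or cardiac contraindication, and found out later, would be missing from both.

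The approved-indications phrase is a second defect. Because it is undefined for an app, two analysts could build different safety sets from the same data.

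**Working it through.** No figure in the protocol depends on the safety set, so there is none to reproduce. The check compares the sections and then asks whether a direction of bias can be derived.

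**1. Who is removed by the eligibility condition?** Criteria are confirmed at Visit 1 (Section 4.4), and only subjects who meet them get a randomization enrollment number (Section 4.5). The condition can therefore bite only on subjects whose ineligibility surfaces later, the case named in Section 3.5. Late discovery is plausible. No test is mandatory (Sections 4.1 and 4.3), laboratory values are collected only when done in routine care, and baseline values other than HbA1c may be up to 3 months old (Section 4.4). Total bilirubin is part of an exclusion criterion in Section 3.4 but is not among the example laboratory items in Section 4.4.

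**2. What kind of subjects are they?** Section 3.4 excludes subjects with drug contraindications (renal and hepatic impairment, NYHA class III or IV, hypersensitivity). It also excludes prior Well Check users, participants in other trials and people with recent weight-loss treatment. Late-found ineligible subjects may therefore include some with a raised chance of abnormal laboratory values or vital signs, and others with no evident extra risk.

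**3. What does the approved-indications test do?**

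- *If the product is the app:* the Synopsis and Section 3.5 support this reading. The protocol states no indication for Well Check. Section 3.6 mentions a marketing authorization of the investigational product but names no indication. The test cannot be applied.
- *If the product is the background drug:* Section 8.8 says that no investigational drug is supplied. Section 3.3 already requires Envlo or Envlomet SR within its approved conditions, and Section 3.4 already excludes its contraindications. The test then largely repeats eligibility.
- *Under either reading:* a single compliant use is enough, so subjects with mixed use stay in.

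**4. Can the direction of bias be derived?** Let f be the share of exposed subjects removed, p_x their abnormality rate and p_r the rate in those retained. The rate in all exposed subjects is

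p = (1 − f) × p_r + f × p_x,

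so the reported rate differs from it by

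p_r − p = f × (p_r − p_x).

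The reported rate is too low only if p_x exceeds p_r, and the difference can never exceed f. The protocol gives none of f, p_x or p_r. The sign is open, because Section 7.2 looks at changes. A subject excluded for a raised liver value may already be abnormal at baseline and so show no new abnormality. The listing is different: any clinically significant abnormality in a removed subject is simply left out.

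For scale only, each 1% of the 480 planned subjects is 480 × 0.01 = 4.8 people.

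**The case against.** The strongest reply is that this is a small matter of wording. Eligibility is screened before enrolment, so few subjects should be lost. The approved-indications phrase removes no identifiable subject if it means the app, and adds little if it means the drug. The intervention is software, and Section 8.8 describes the study as adding no risk beyond routine care. Laboratory data come only from routine practice, so what happens to be measured will probably shape the safety tables more than a few exclusions. The excluded subjects' records remain in the eCRF.

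Most of this stands as a limit on size. It also disposes of some stronger readings:

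- *That the rule removes the patients most at risk.* Section 3.4 mixes safety-relevant exclusions with others that are not, and the protocol does not show which would be found late.
- *That abnormality rates are understated.* Step 4 shows that the sign cannot be determined.
- *That the arms are affected unequally.* Test-arm physicians review linked data and control-arm physicians do not (Section 4.4), so discovery could differ. The protocol does not say that it does.

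The reply does not justify the rule itself. The protocol states a condition that removes exposed subjects from the safety set, and it offers no all-exposed alternative and no separate listing. Safety is also not purely descriptive, since Section 7.2 applies mixed models or GEE to changes in vital signs and laboratory values.

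**Conclusion.** The point holds as a defect in the definition of the safety set, and it should be corrected. By rule, enrolled and exposed subjects later found ineligible are left out, and the approved-indications condition is either inoperable or largely redundant. On that condition the safety set is also worded more narrowly than the efficacy set.

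The size is unknown. A reader might assume that 2% to 10% of 480 subjects are affected, which gives 480 × 0.02 = 9.6 (about 10) to 480 × 0.10 = 48. The protocol gives no basis for that range, so it should not be read as an estimate. The direction of any bias is equally undetermined. The primary HbA1c analysis and the sample size do not use this set.

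The conclusion assumes that the safety tables and the listing are produced on the safety set. That is the natural reading of Section 7.2, although the laboratory and vital-sign paragraphs do not repeat it.

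**What to change.** Redefine the safety set in Section 7.2 as all enrolled subjects who installed or used Well Check at least once, analysed by the arm assigned to their clinic, regardless of ineligibility found later. Delete the eligibility condition and the approved-indications phrase. Replace the requirement for safety evaluations with a statement that each parameter is summarised in the subjects who have data for it.

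Installation is the practical criterion. It is scheduled for Visit 1, whereas login days are scheduled only for the close-out visit and may be missing for subjects who withdraw.

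The cost is a sentence or two in Section 7.2 and IRB approval of the amendment (Section 8.5). No new data are needed, because Section 3.5 already has data up to withdrawal entered in the eCRF. No treatment or eligibility rule changes.
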